## SUMMARY

**Background:** Each year, thousands of children experience cardiac arrests, requiring immediate and accurate resuscitation for favorable outcomes. However, adherence to American Heart Association (AHA) advanced life support guidelines remains suboptimal, hindered by cognitive and communication challenges in high-stress situations. Unfortunately, despite recurrent training, healthcare providers struggle to maintain consistent adherence to these guidelines, resulting in only 20-40% of providers achieving guideline-compliant resuscitation care. With merely 40% of children surviving to hospital discharge after experiencing in-hospital (IHCA), there is an urgent need to design, evaluate, and implement innovative strategies to enhance the provision of advanced life support care. To date, the resuscitation room environment has received little attention, with few studies exploring how modifying the clinical environment could enhance clinical performance. Supporting resuscitation teams by integrating decision support technology represents a unique opportunity. To address this problem, we will assess the InterFACE-AR system. The system aims to provide individualized, real-time, role-specific decision support to the team leader and medication nurse through optically see-through augmented reality (AR) headsets and by displaying a dynamic roadmap for patient care on a large LCD screen in the resuscitation room, controlled by a mobile tablet app.

**Objective:** To assess whether the use of InterFACE-AR (intervention group) improves adherence to AHA PALS guidelines, when compared to groups using the AHA PALS pocket reference card (control).

**Method:** An open-label, prospective, multicenter, cluster randomized clinical trial comparing InterFACE-AR to conventional methods in adherence to AHA PALS guidelines during simulated pediatric IHCA scenarios.

**Participants:** 54 physicians and nurses, in teams of seven, in two tertiary hospitals.

**Intervention:** Randomization centralized with a 1:1 ratio to either InterFACE-AR support (intervention; n=27) or conventional method (control; n=27). Each participant will undergo a 12-min standardized realistic pediatric IHCA resuscitation scenario.

**Outcomes:** The primary outcome is the time to first dose of epinephrine, defined as the interval in seconds from recognition of CA at the start of the scenario to completion of epinephrine injection. Secondary outcomes are times to CPR initiation, defibrillation, drug delivery, airway securing, the rate of medication errors, chest compression fraction and peri-shock pause duration. User experience (UEQ), and technology acceptance (TAM) will be also assessed among the intervention group.

**Perspectives:** This project has the potential to exceed current clinical practice standards and reshape resuscitation care by harnessing immersive technology and fostering interdisciplinary collaboration. Our knowledge translation strategy through publications and international organizations should ensure widespread dissemination of findings, catalyzing a transformative shift in digital health applications for pediatric resuscitation worldwide. Our project's alignment with AHA resuscitation guidelines may lead to future adaptations for adult cardiopulmonary resuscitation.

## **1. Introduction**

### **1.1 Background and Rationale**

Each year, thousands of children experience cardiopulmonary arrests (CA), requiring immediate and accurate resuscitation for favorable outcomes. However, adherence to American Heart Association (AHA) advanced life support guidelines remains suboptimal, hindered by cognitive and communication challenges in high-stress cardiopulmonary resuscitation (CPR) situations. To address this problem, we will assess a novel augmented reality (AR)-assisted digital health solution designed to offer personalized, real-time decision support for team leaders and medication nurses, while concurrently optimizing team situational awareness and communication by projecting a dynamic care roadmap onto a large screen in the resuscitation room, controlled via a mobile tablet app.

The solution comprises three essential digitally interconnected elements: 1) a mobile app that presents clinical algorithms alongside patient data, guiding the resuscitation team through step-by-step procedures, 2) a giant screen that displays real-time patient information and task progress for the entire resuscitation team, and 3) augmented reality headsets worn by team members, providing role-specific guidance and decision support based on data collected by the app.

In this trial, we will assess, amongst pediatric healthcare teams, whether the use of the AR-assisted tool improves adherence to AHA resuscitation guidelines and performance, when compared to groups using the AHA Paediatric Advanced Life Support (PALS) pocket reference cards (control) in an open-label, prospective, multicenter, cluster randomized (1:1 ratio) clinical trial. Resuscitation teams of physicians and nurses will be asked to manage simulated pediatric in-hospital cardiac arrest (IHCA) scenarios using either an AR-assisted tool or conventional AHA PALS pocket cards. Each team will comprise three participants assigned to the roles of 1) Team Leader (a physician), 2) Charting Nurse, and 3) Medication Nurse, with two CPR Providers, an Airway Provider, and a Bedside Provider role filled by research actors.

### **1.2 Previous Work Justifying This Trial**

In the past, our multicenter studies have successfully influenced the use of debriefing tools for AHA instructors, the implementation of feedback devices for CPR skills training, and the integration of CPR coaching across AHA's life support courses (e.g. BLS, PALS, ACLS). A randomized controlled trial by our team, recognized as pioneering in a scoping review, showed that an AR device delivering real-time clinical guidance to the team leader during simulated pediatric IHCA reduced defibrillation dosing errors by 53% compared to AHA pocket cards. However, reliance on the team leader alone

increased workload and did not improve critical timings for epinephrine or defibrillation. Additionally, the system's limitations in situating the current action within the entire resuscitation process, coupled with its small size, posed major challenges to effectively displaying CPR algorithms during pediatric IHCA. Building on these lessons, we developed Guiding Pad, a mobile app used by the charting nurse to deliver interactive, role-specific guidance and cognitive aids aligned with PALS algorithms. In a single-center RCT, Guiding Pad significantly reduced time to defibrillation, decreased medication and energy dose errors, and improved adherence to PALS guidelines by ~70% compared to pocket cards. Integrated with a large display - called InterFACE (Interconnected and Focused Mobile Applications in the patient Care Environment) - the system supports real-time team situational awareness and communication. This work aligns with the AHA's 2024 call to advance health technology and supports our aim to leverage AR to improve pediatric resuscitation outcomes.

### 1.3 Evidence Before the Current Project

We searched PubMed, Web of Science, EMBASE and the Cochrane Library for peer-reviewed articles on AR in emergency medicine, spanning from inception to March 18, 2024, without language or age restrictions. MeSH terms "Cardiopulmonary resuscitation", "Emergency Medicine" and "Augmented reality" were explored and connected by Boolean operators. Out of 84 articles retrieved, 34 were excluded based on title and an additional 24 on abstract review. Among the 26 studies identified, three thematic categories emerged; AR in resuscitation education (n=15), prehospital and disaster medicine (n=5), and review articles (n=5). But we only identified our previous single-center trial as focusing on the clinical application of AR to aid adherence to AHA PALS algorithms. Most of the studies used Google Glass and Microsoft HoloLens as AR devices, with the latter now incorporating depth sensing and human gesture recognition, representing the latest trend in AR.

## 2. Methods

### 2.1 Study Objectives

In the proposed study, we aim to evaluate the effect of an enhanced system, InterFACE-AR (see Point 2.2 below), which significantly evolves the initial InterFACE version to leverage the capabilities of AR, on key performance metrics, including time to epinephrine and adherence to AHA guidelines during simulated pediatric IHCA scenarios. We also aimed to explore the usability and acceptance of the InterFACE-AR system amongst participants.

### 2.2 The InterFACE-AR Decision Support System

This system integrates three interconnected components (**Figure 1**): (1) The Guiding-Pad app, operated by the charting nurse. It displays the appropriate resuscitation algorithm and clinical status, allowing for the charting nurse to input data in real-time. (2) Clinical data is broadcast to the TeamScreen, a shared

display that provides the resuscitation team with a structured, chronological overview of the current algorithm, clinical guidance (current and next steps), and a summary of ongoing and completed tasks. (3) Simultaneously, two AR headsets (Microsoft HoloLens 2™) deliver role-specific, real-time clinical guidance to the team leader and medication nurse, such as prompts for drugs and defibrillation (for the team leader) or suggested medication and doses (for the medication nurse).

[figure not shown]

**Figure 1.** InterFACE-AR system components

## 2.3 Scientific Aims

**Primary scientific aim:** To determine amongst pediatric healthcare teams whether use of InterFACE-AR (intervention group) reduces the time from loss-of-pulse recognition to first epinephrine administration, compared with standard practice using the AHA PALS pocket reference cards (control).

**Second scientific aim:** To assess whether the use of InterFACE-AR improves resuscitation performance and adherence to AHA PALS guidelines, compared with standard practice.

## 2.4 Trial Design and Setting

We plan to conduct an open-label, prospective, simulation-based, multicenter, cluster randomized clinical trial at both Geneva (Switzerland) and Calgary (Canada) Children's Hospitals. Simulation-based research confers the advantage of answering research questions without risk of harm to patients. The scenarios will be conducted in situ at the institutional simulation centers. We will compare team performance using the InterFACE-AR supportive tool (intervention) or conventional AHA PALS pocket reference cards (control) during standardized pediatric IHCA. Participants will be recruited to the study in teams of three, comprised of a team leader, charting nurse, and medication nurse. Additionally, four trained research actors will fill the scripted roles of CPR provider / CPR Coach (2

actors, alternating roles), an airway provider, and a Bedside Provider to make a resuscitation team of 7 providers. The actor will be trained with methodology successfully used in prior multicenter trials. Participant teams will manage one CA simulation scenario (see below), using the specific trial intervention assigned during randomization. No changes will be made to the apps and devices during the study. **Figure 2** shows the trial flow chart and **Figure 3** the trial checklist. As this simulation-based study enrolls only healthcare professionals, there will be no patient or public involvement in the design, conduct, or reporting of the trial. The trial will be conducted according to appropriate guidelines and follow the 2025 Consolidated Standards of Reporting Trials (CONSORT) reporting guideline. The present trial protocol adheres to the SPIRIT 2025 checklist (see **Appendix** at the end of the protocol). It is our intention to present the results at scientific congresses and to publish the results in a peer-reviewed journal, irrespective of the magnitude or direction of effect.

[figure not shown]

**Figure 2. Trial flow chart.**

PEA, pulseless electrical activity; pVT, pulseless ventricular tachycardia; TAM, technology acceptance model; UEQ, user experience questionnaire; VF, ventricular fibrillation.

## 2.5 Participants and Eligibility Criteria

Eligible team leaders will be attending physicians, fellows, senior residents, or physician assistants in emergency medicine, pediatric emergency medicine, general pediatrics, pediatric critical care, or pediatric anesthesia of both pediatric hospitals. Eligible medication and charting nurses will be nurses

in pediatric emergency medicine, general pediatrics, or pediatric intensive care units. All participants will be required to have completed prior basic life support training. Exclusion criteria: (1) previously participated in the design, development, or usability assessment of the system; or (2) unable to perform tasks required of the role.

## **2.6 Recruitment Process**

To ensure sufficient subject enrolment for reaching the target sample size on the day of participation, teams will be randomly recruited and scheduled weeks prior to the study commencement by a blinded non-investigator. To mitigate preparation bias, they will be informed about the upcoming simulation study without knowledge of its objectives and outcomes. In cases of participant unavailability, the research team will arrange for a replacement.

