## 7.2 Group Allocation

Randomization will be conducted in a 1:1 ratio at the level of the team and stratified by study site using an online random number generator. Randomization will be conducted in blocks of two to ensure equal distribution of teams across study arms. Study packages will be prepared with opaque envelopes to achieve allocation concealment. Sequentially numbered recruitment packages provided for each site will contain unique identifier codes for participants, along with study arm assignments. Personnel who enroll participants and those who assign participants to interventions will have no advance access to the sequence. On the trial day, the principal investigators or delegated investigators will obtain written informed consent from participants before any study procedures, and selection criteria will be checked prior to participation in the study. Immediately after written consent, the authorized staff will access only the assignment function to obtain the participant's allocation. Assignment will occur once per participant, with audit trails documenting day and time.

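### Replacements are arranged by the research team with no selection rule, and blocks of two within site mean some can be chosen with the arm known

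*Combined protocol and SAP*

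**What the plan says.** Section 2.6 describes recruitment in these words: "teams will be randomly recruited and scheduled weeks prior to the study commencement by a blinded non-investigator". The same paragraph ends: "In cases of participant unavailability, the research team will arrange for a replacement". It does not say where the substitute comes from, whether grade or experience is matched, whether the person choosing is blinded, or by when the substitution must be made.

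Section 7.2 supplies the allocation safeguards: "Study packages will be prepared with opaque envelopes to achieve allocation concealment", and "Personnel who enroll participants and those who assign participants to interventions will have no advance access to the sequence". On the trial day consent is taken and "selection criteria will be checked prior to participation in the study". One exclusion in Section 2.5 is a matter of judgement: "unable to perform tasks required of the role". Assignment then follows: "Immediately after written consent, the authorized staff will access only the assignment function to obtain the participant's allocation".

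Section 7.2 randomizes teams 1:1, stratified by site, and adds: "Randomization will be conducted in blocks of two to ensure equal distribution of teams across study arms". Section 2.4 describes the trial as open-label.

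Section 6.2 keeps data from participants who discontinue or deviate in the intention-to-treat dataset. The closing paragraph of Section 7.4.6 specifies complete-case analysis. Neither mentions substitution.

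**The concern.** The random draw by a blinded person keeps team composition independent of anyone's expectations about the trial. A substitution made at discretion by the research team bypasses that protection. Eligible leaders range from senior residents and physician assistants to attending physicians, so the choice of substitute could plausibly affect time to first epinephrine.

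Discretion does little harm to the comparison if the person choosing cannot know the arm. If the arm is known or can be deduced, the choice can favour one arm, even unintentionally. With nine teams per arm, one or two such teams are a visible share of the data.

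**Working it through.** **Inputs.** Section 7.1: 18 teams, 9 per arm; target reduction 35 s; IQR 139 to 173 s. Section 7.2: 1:1 by team, stratified by site, blocks of two. Section 2.4: two sites. The split of teams between sites is not stated, and Section 9.4 allows recruitment to be moved between sites. The replacement rate and the effect of a substitute on a team's time are not stated, so both are assumed below.

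**Plan's own figure used as a scale.** SD = (173 − 139)/1.35 = 25.2 s. This reproduces Section 7.1.

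**When could the person choosing know the arm?**

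1. *Before the envelope is opened.* In a block of two, the second team's arm follows from the first team's. In an open-label trial, site staff see the first team's arm. The number of deducible teams is the sum over sites of floor(n/2):
   - Both sites odd (for example 9 + 9): 4 + 4 = 8 of 18 (44%).
   - Both sites even (for example 10 + 8): 5 + 4 = 9 of 18 (50%).
   - Expected correct guesses over all teams: (8 + 10 × 0.5)/18 = 72%, or (9 + 9 × 0.5)/18 = 75%, against 50% with no predictability.

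   Lack of access to the sequence does not prevent this deduction.

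2. *After allocation.* Section 3.2 places orientation after randomization, and the intervention arm's extra part lasts 10 + 5 + 4 = 19 minutes. Section 8.2 foresees dizziness, motion sickness with AR and withdrawals. Only the intervention arm wears headsets, so headset-related loss would be one-sided. No text says that a member lost in this window is replaced, and none forbids it. Figure 3 (Section 5) lists AR orientation at enrolment, before randomization, so the length of the window depends on which passage is followed.

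**Illustration of size (assumed effects).** Suppose one substitute makes a team 25 to 35 s faster, that is, by about one SD up to the whole target effect.
- Shift in that arm's mean: 25/9 = 2.8 s to 35/9 = 3.9 s.
- Share of the target: 2.8/35 = 8% to 3.9/35 = 11%. Two such teams: 16 to 22%.
- Standard error of the difference: 25.2 × √(2/9) = 11.9 s. One team's shift is therefore 0.23 to 0.33 of a standard error.

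**Second illustration (assumed effects, no true difference).** Nine deducible teams, each with probability f of a replacement that moves its time by d seconds in favour of the intervention. About half of these teams fall in each arm, so the expected spurious difference is f × d. Type I error comes from 20,000 simulated trials, with a two-sided t-test standing in for the planned permutation test.

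| f | d = 10 s: bias, type I error | d = 20 s: bias, type I error |
|---|---|---|
| 10% | 1.0 s, 4.8% | 2.0 s, 5.4% |
| 25% | 2.5 s, 5.4% | 5.0 s, 6.6% |
| 50% | 5.0 s, 6.8% | 10 s, 11.5% |
| 100% | 10 s, 11.5% | 20 s, 30.3% |

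Rare replacement leaves the error rate near 5%. Material inflation needs frequent replacement that is consistently selective.

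**The case against.** The strongest reply is that the replacement sentence closes a paragraph about scheduling weeks ahead. Its natural reading is a person who cannot attend, and that person is replaced before the team's arm is revealed. Section 7.2 and Figure 3 place consent and eligibility before assignment, with opaque envelopes and no advance access. Loss during a session is dealt with elsewhere, and not by substitution: Section 2.7 pauses or terminates and reports, Section 6.2 records and retains the data, and Section 8.2 logs withdrawals. Section 2.8 also mentions standard operating procedures, which may contain a rule but are not part of these documents.

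Most of this stands. A reader might infer that an unblinded research team routinely picks substitutes with the arm known, or that people who cannot tolerate the headset will be swapped out, contrary to Section 6.2. The documents support neither inference. They never call the research team unblinded at the time of replacement, and no passage links the replacement sentence to in-session dropout.

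The reply does not answer the deduction from blocks of two, which operates before the envelope is opened and despite perfect concealment. Nor does it supply a selection rule or an explicit bar on late substitution.

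**Conclusion.** The point holds in a limited form. The plan protects the initial draw but leaves substitution to discretion, by people not stated to be blinded. For 8 or 9 of 18 teams the arm can be deduced before allocation, given that site staff know the block size and the previous team's arm. Substitution after allocation is possible under the text, but it is not what the text describes.

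The actual bias cannot be determined. The shift of 2.8 to 3.9 s per selected team (8 to 11% of the target) rests on an assumed 25 to 35 s gain from changing one of three members, which is large. This is a weakness in design that is cheap to remove; it is not evidence that allocation concealment is broken.

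**What to change.** In Section 2.6, have the blinded non-investigator draw a random reserve list by site and role, and by leader grade where feasible, when teams are scheduled. Substitutes are taken in order from that list. Because nobody then chooses the substitute, a deducible arm can no longer guide the choice, even with blocks of two.

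In Section 7.2, require eligibility and any substitution to be complete for the whole team before its envelope is opened.

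In Sections 6.2 and 7.4, state that a team losing a member after allocation stays in its assigned arm, with the event logged and reported by arm. Also say how a team left with no epinephrine time is handled. A bare ban on late replacement is not enough: complete-case analysis would drop that team, which is 1 of 9 (11%) of an arm, and headset-related losses would leave the primary result unnoticed.

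The cost is a few sentences and a list made in the existing draw. The downside is that an occasional session must be rescheduled, or that one team may lack a primary outcome.

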## **2.7 Criteria for Discontinuing or Modifying Interventions**

We do not anticipate modification or discontinuation of the allocated simulation condition for trial participants. Each session will follow the planned protocol for a full 60-minute scenario per participant, scheduled several weeks in advance to ensure availability of the participants without repercussions on their normal duty. All participants will have prior authorization from their hierarchy to attend. As a simulation study with high-fidelity manikins and no patient involvement, the intervention is highly feasible and carries minimal risk. Only in exceptional circumstances such as an unforeseen technical failure of the simulator/AR device or a participant-initiated request may the session be briefly paused or, if necessary, terminated and reported.

## **2.8 Strategies to Improve Adherence**

We don't anticipate any major issues with adherence based on our prior experience conducting simulation-based multicenter studies. We will implement a multifaceted approach to ensure compliance with our research protocol: (1) development of standard operating procedures and a research protocol guide; (2) submission of data from at least one pilot session per site, which will be reviewed for protocol adherence before recruitment; (3) monthly review of study data and videos for protocol adherence and quality control. Recruitment process to ensure adherence was described in section 2.4 above.

